**Level of Knowledge on Soil-transmitted helminths**

| **i** | **A-** Do you know how intestinal worms / parasites are transmitted? | | | | \| **⃞** \| Yes \| (1) \|  \| **⃞** \| No \| (0) \| \| --- \| --- \| --- \| --- \| --- \| --- \| --- \| | |
| --- | --- | --- | --- | --- | --- | --- | --- | --- | --- | --- | --- | --- | --- |
|  | **B-** If yes, how?   \| **⃞** *Not applicable (NA)* \| \| --- \| | \| 1) \|  \| \| --- \| --- \| \| 2) \|  \| \| 3) \|  \| \| 4) \|  \| | | | | |
| **II** | **A**- Do you know why worms / parasites are bad for your health? | | | | \| **⃞** \| Yes \| (1) \|  \| **⃞** \| No \| (0) \| \| --- \| --- \| --- \| --- \| --- \| --- \| --- \| | |
|  | **B-** If yes, why are they bad?   \| **⃞** *Not applicable (NA)* \| \| --- \| | | | \| 1) \|  \| \| --- \| --- \| \| 2) \|  \| \| 3) \|  \| \| 4) \|  \| | | |
| **III** | **A**- Do you know how you can avoid getting these worms / parasite infection? | | | | | \| **⃞** \| Yes \| (1) \|  \| **⃞** \| No \| (0) \| \| --- \| --- \| --- \| --- \| --- \| --- \| --- \| |
|  | **B-** If yes, how?   \| **⃞** *Not applicable (NA)* \| \| --- \| | | \| 1) \|  \| \| --- \| --- \| \| 2) \|  \| \| 3) \|  \| \| 4) \|  \| | | | |

**Questionnaire on risk factors**

| **7** | | **A-** Where do you live?  **B-** Where do you live (street, passage, sector, block, lot)? | | \| Community: ............................................... \| **⃞** *Don’t know* (99) \| \| --- \| --- \| \| Address: .................................................  .................................................................... \| **⃞** *Don’t know* (99)  **⃞** *Not applicable* (NA) \| | |
| --- | --- | --- | --- | --- | --- | --- | --- | --- | --- |
| **8** | | Is your house made out of noble or rustic materials? | | \| **⃞** \| Noble \| (1) \| **⃞** \| Rustic \| (0) \| **⃞** \| *Don’t know* \| (99) \| \| --- \| --- \| --- \| --- \| --- \| --- \| --- \| --- \| --- \| | |
| **9** | | In your house, do you Cook with gas, kerosene, coal, o wood? | | \| **⃞** \| Gas \| (0) \| **⃞** \| Coal \| (2) \| **⃞** \| Others____ \| (4) \| \| --- \| --- \| --- \| --- \| --- \| --- \| --- \| --- \| --- \| \| **⃞** \| Kerosene \| (1) \| **⃞** \| Wood \| (3) \| **⃞** \| *Don’t know* \| *(99)* \| | |
| **10** | | Do you have electricity at your house? | | \| **⃞** \| Yes \| (1) \| **⃞** \| No \| (0) \| **⃞** \| *Don’t know* \| (99) \| \| --- \| --- \| --- \| --- \| --- \| --- \| --- \| --- \| --- \| | |
| **11** | | Does your family own a radio? | | \| **⃞** \| Yes \| (1) \| **⃞** \| No \| (0) \| **⃞** \| *Don’t know* \| (99) \| \| --- \| --- \| --- \| --- \| --- \| --- \| --- \| --- \| --- \| | |
| **12** | | Does your family own a television? | | \| **⃞** \| Yes \| (1) \| **⃞** \| No \| (0) \| **⃞** \| *Don’t know* \| (99) \| \| --- \| --- \| --- \| --- \| --- \| --- \| --- \| --- \| --- \| | |
| **13** | | **A-** Do you have potable water in your house? | | \| **⃞** \| Yes \| (1) \| **⃞** \| No \| (0) \| **⃞** \| *Don’t know* \| (99) \| \| --- \| --- \| --- \| --- \| --- \| --- \| --- \| --- \| --- \| | |
|  |  | **B-** If not, where do you get your water from?   \| **⃞** *Not applicable (NA)* \| \| --- \| | | \| **⃞** \| Neighbour \| (0) \|  \| **⃞** \| Tank \| (4) \| \| --- \| --- \| --- \| --- \| --- \| --- \| --- \| \| **⃞** \| River \| (1) \|  \| **⃞** \| Public fountain \| (5) \| \| **⃞** \| Well \| (2) \|  \| **⃞** \| Others___________ \| (6) \| \| **⃞** \| Truck \| (3) \|  \| **⃞** \| *Don’t know* \| (99) \| | |
| **14** | | In your house do you drink your water directly or do you treat it (boiling or bleaching)? | | \| **⃞** \| Directly \| (1) \| **⃞** \| Treated \| (0) \| **⃞** \| *Don’t know* \| (99) \| \| --- \| --- \| --- \| --- \| --- \| --- \| --- \| --- \| --- \| | |
| **15** | | At home, is your latrine inside or outside the house? | | \| **⃞** \| Inside \| (1) \| **⃞** \| Outside \| (0) \| **⃞** \| *Don’t know* \| (99) \| \| --- \| --- \| --- \| --- \| --- \| --- \| --- \| --- \| --- \| | |
| **16** | | Is your latrine connected with the sewage system, a ditch, the river, or a well? | | \| **⃞** \| Sewage \| (0) \| **⃞** \| River \| (2) \| \| --- \| --- \| --- \| --- \| --- \| --- \| \| **⃞** \| Ditch \| (1) \| **⃞** \| Well \| (3) \| \| **⃞** *Don’t know* (99) \| \| \| \| \| \| | |
| **17** | | Do you bath in the Itaya river – always, sometimes, or never? | | \| **⃞** \| Always \| (0) \| **⃞** \| Never \| (2) \| \| --- \| --- \| --- \| --- \| --- \| --- \| \| **⃞** \| Sometimes \| (1) \| **⃞** \| *Don’t know* \| (99) \| | |
| **18** | | Do you defecate (#2) in the open air – always, sometimes, or never? | | \| **⃞** \| Always \| (0) \| **⃞** \| Never \| (2) \| \| --- \| --- \| --- \| --- \| --- \| --- \| \| **⃞** \| Sometimes \| (1) \| **⃞** \| *Don’t know* \| (99) \| | |
| **19** | | Do you use toilet paper to wipe your bum after you have defecated (#2) – always, sometimes, or never? | | \| **⃞** \| Always \| (0) \| **⃞** \| Never \| (2) \| \| --- \| --- \| --- \| --- \| --- \| --- \| \| **⃞** \| Sometimes \| (1) \| **⃞** \| *Don’t know* \| (99) \| | |
| **20** | | **A-** Do you wash your hands after going to the bathroom – always, sometimes, or never?  **B-** How do you wash your hands after going to the bathroom – with water only or with soap and water?   \| **⃞** *Not applicable (NA)* \| \| --- \|   **C-** If with soap and water, do you use soap always, sometimes, or never?   \| **⃞** *Not applicable (NA)* \| \| --- \| | | \| **⃞** \| Always \| (0) \| **⃞** \| Never \| (2) \| \| --- \| --- \| --- \| --- \| --- \| --- \| \| **⃞** \| Sometimes \| (1) \| **⃞** \| *Don’t know* \| (99) \|  \| **⃞** \| Water \| (0) \| **⃞** \| Soap and water \| (1) \| **⃞** \| *Don’t know* \| (99) \| \| --- \| --- \| --- \| --- \| --- \| --- \| --- \| --- \| --- \|  \| **⃞** \| Always \| (0) \| **⃞** \| Never \| (2) \| \| --- \| --- \| --- \| --- \| --- \| --- \| \| **⃞** \| Sometimes \| (1) \| **⃞** \| *Don’t know* \| (99) \| | |
| **21** | | **A-** Do you wash your hands before eating – always, sometimes, or never?  **B-** How do you wash your hands before eating – with water only or with soap and water?   \| **⃞** *Not applicable (NA)* \| \| --- \|   **C-** ¿ If with soap and water, do you use soap always, sometimes, or never?   \| **⃞***Not applicable (NA)* \| \| --- \| | | \| **⃞** \| Always \| (0) \| **⃞** \| Never \| (2) \| \| --- \| --- \| --- \| --- \| --- \| --- \| \| **⃞** \| Sometimes \| (1) \| **⃞** \| *Don’t know* \| (99) \|  \| **⃞** \| Water \| (0) \| **⃞** \| Soap and water \| (1) \| **⃞** \| *Don’t know* \| (99) \| \| --- \| --- \| --- \| --- \| --- \| --- \| --- \| --- \| --- \|  \| **⃞** \| Always \| (0) \| **⃞** \| Never \| (2) \| \| --- \| --- \| --- \| --- \| --- \| --- \| \| **⃞** \| Sometimes \| (1) \| **⃞** \| *Don’t know* \| (99) \| | |
| **22** | | **A-** What is your favourite fruit that you eat?  **B-** Do you was your fruits before eating - always, sometimes, or never? | | Fruit: ………………………………….   \| **⃞** \| Never \| (0) \| **⃞** \| Always \| (2) \| \| --- \| --- \| --- \| --- \| --- \| --- \| \| **⃞** \| Sometimes \| (1) \| **⃞** \| *Don’t know* \| (99) \| | |
| **26** | | Do you walk barefoot - always, sometimes, or never? | | \| **⃞** \| Never \| (0) \| **⃞** \| Always \| (2) \| \| --- \| --- \| --- \| --- \| --- \| --- \| \| **⃞** \| Sometimes \| (1) \| **⃞** \| *Don’t know* \| (99) \| | |
| **27** | | When you are at home do you prefer to use sandals or shoes? | | \| **⃞** \| Does not use any \| (0) \| **⃞** \| Shoes \| (2) \| \| --- \| --- \| --- \| --- \| --- \| --- \| \| **⃞** \| Sandals \| (1) \| **⃞** \| *Don’t know* \| (99) \| | |
| **28** | | In which activities of the day are you barefoot?   \| **⃞** *Not applicable (NA)* \| \| --- \| | | A- Activity: ………..………………………………….  B- Activity: ………..………………………………….  C- Activity: ………..…………………………………. | |
| **29** | | **A-** Did your parents or your professor gave you a deworming pill?  **B-** If yes, when was the last time they gave you such deworming pill? | | \| **⃞** \| Yes \| (1) \| **⃞** \| No \| (0) \| **⃞** \| *Don’t know* \| (99) \| \| --- \| --- \| --- \| --- \| --- \| --- \| --- \| --- \| --- \|  \|  \| Months \| **⃞** \| More than a year (13) \| **⃞**  **⃞** \| *Don’t know (99)*  Not applicable (NA) \| \| --- \| --- \| --- \| --- \| --- \| --- \| | |
| **30** | | **A-** How many people live in your house? Enumerate them…  **B-** How many children younger than 12 years old live in your house? | | \|  \| People  (including you) \| **⃞** \| *Don’t know (99)* \| \| --- \| --- \| --- \| --- \| \|  \| Children \| **⃞** \| *Don’t know (99)* \| | |
|  | **Comments:** | |  | |  |
|  |  | | | |  |
|  |  | | | |  |

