**Secondary**

The following secondary research objectives will also be addressed: i) to determine intervention effects on absenteeism rates; ii) to assess gender-specific determinants of STH infection, re-infection and absenteeism rates; iii) to measure STH species-specific cure rates and egg reduction rates; and iv) to examine behavioural and social determinants of STH infection, re-infection and absenteeism rates.

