**Health hygiene education intervention**

Lack of knowledge on the transmission and prevention methods of STH infections is common factor in affected population groups of Latin America [27]. Therefore, the specific objectives of the health hygiene education intervention are:

i) To implement a gender-specific health hygiene education strategy which will result in a sustainable intervention that encourages the pro-active role of both teachers and students.

ii) To encourage changes in attitudes and practices with the aim of keeping the level of parasite infection low, through increased knowledge.

iii) To identify modifiable gender-specific behavioural and social determinants which favour the acquisition and transmission of STH infections to inform prevention activities.

Workshops will be organized for and by Grade 5 teachers to train them on the health hygiene education strategy. The education material will be provided by the Pan American Health Organization (in Spanish) and will be adapted to the local culture. The health hygiene education intervention will take into account the gender-specific perceptions, values, social constructs, and beliefs of students and teachers relevant to STH infections in order to maximize behavioural changes. After the workshop, Grade 5 teachers will be able to implement the health hygiene education intervention in their classroom and engage their students. Bi-monthly visits with the teacher by our research team and once monthly with the class will be performed to monitor the application of the education program during the 4-month follow-up period. Specifically, the intention of the health hygiene education program is to modify key gender-specific modifiable behavioural determinants that have been shown to be associated with STH infections from our review of the literature:

i) Not using soap for hand washing [28-30]

ii) Not hand washing (no reference to the use of soap) [31-33]

iii) Eating unpeeled or unwashed fruits [31, 34]

iv) Walking barefoot [30, 33]

v) Open air defecation [33-35]

vi) General unhygienic behaviours [36]

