| **14** | | ¿En casa tomas agua directo o tratada (hervida o clorada)? | | \| **⃞** \| Directo \| (1) \| **⃞** \| Tratada \| (0) \| **⃞** \| *No sabe* \| (99) \| \| --- \| --- \| --- \| --- \| --- \| --- \| --- \| --- \| --- \| | |
| **15** | | ¿Tu baño se ubica adentro o afuera de tu casa? | | \| **⃞** \| Adentro \| (1) \| **⃞** \| Afuera \| (0) \| **⃞** \| *No sabe* \| (99) \| \| --- \| --- \| --- \| --- \| --- \| --- \| --- \| --- \| --- \| | |
| **16** | | ¿Tu baño está conectado a tubo de desagüe, a caño, a río, o a pozo ciego? | | \| **⃞** \| Desagüe \| (0) \| **⃞** \| Río \| (2) \| \| --- \| --- \| --- \| --- \| --- \| --- \| \| **⃞** \| Caño \| (1) \| **⃞** \| Pozo ciego o silo \| (3) \| \| **⃞** *No sabe* (99) \| \| \| \| \| \| | |
| **17** | | ¿Te bañas en el río Itaya – siempre, a veces, o nunca? | | \| **⃞** \| Siempre \| (0) \| **⃞** \| Nunca \| (2) \| \| --- \| --- \| --- \| --- \| --- \| --- \| \| **⃞** \| A veces \| (1) \| **⃞** \| *No sabe* \| (99) \| | |
| **18** | | ¿Haces el dos en campo abierto (huerta o patio) - siempre, a veces, o nunca? | | \| **⃞** \| Siempre \| (0) \| **⃞** \| Nunca \| (2) \| \| --- \| --- \| --- \| --- \| --- \| --- \| \| **⃞** \| A veces \| (1) \| **⃞** \| *No sabe* \| (99) \| | |
| **19** | | ¿Te limpias con papel higiénico cuando haces el dos - siempre, a veces, o nunca? | | \| **⃞** \| Siempre \| (0) \| **⃞** \| Nunca \| (2) \| \| --- \| --- \| --- \| --- \| --- \| --- \| \| **⃞** \| A veces \| (1) \| **⃞** \| *No sabe* \| (99) \| | |
| **20** | | **A-** ¿Te lavas las manos después de ir al baño – siempre, a veces, o nunca?  **B-** ¿Cómo te lavas las manos después de ir al baño -con agua sola o jabón y agua?   \| **⃞** *No aplica (NA)* \| \| --- \|   **C-** ¿Si es con jabón, lo usas siempre, a veces, o nunca?   \| **⃞** *No aplica (NA)* \| \| --- \| | | \| **⃞** \| Siempre \| (0) \| **⃞** \| Nunca \| (2) \| \| --- \| --- \| --- \| --- \| --- \| --- \| \| **⃞** \| A veces \| (1) \| **⃞** \| *No sabe* \| (99) \|  \| **⃞** \| Agua \| (0) \| **⃞** \| Jabón y agua \| (1) \| **⃞** \| *No sabe* \| (99) \| \| --- \| --- \| --- \| --- \| --- \| --- \| --- \| --- \| --- \|  \| **⃞** \| Siempre \| (0) \| **⃞** \| Nunca \| (2) \| \| --- \| --- \| --- \| --- \| --- \| --- \| \| **⃞** \| A veces \| (1) \| **⃞** \| *No sabe* \| (99) \| | |

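### Questionnaire items 15 and 16 assume that every home has a latrine and give a child without one no answer that applies

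*Protocol*

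**What the plan says.** Annex 6 (English questionnaire), risk-factor section, item 15 asks "At home, is your latrine inside or outside the house". The boxes are Inside (1), Outside (0) and Don't know (99). Item 16 asks "Is your latrine connected with the sewage system, a ditch, the river, or a well". Its boxes are Sewage (0), Ditch (1), River (2), Well (3) and Don't know (99). Annex 5 (Spanish) asks "Tu baño se ubica adentro o afuera de tu casa" and "Tu baño está conectado a tubo de desagüe, a caño, a río, o a pozo ciego", with the same structure of answers.

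Two rows further on, item 18 asks "Do you defecate (#2) in the open air – always, sometimes, or never" (Spanish: "Haces el dos en campo abierto (huerta o patio) - siempre, a veces, o nunca"). Its boxes are always (0), sometimes (1), never (2) and don't know (99).

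Secondary objective iv is "to examine behavioural and social determinants of STH infection, re-infection and absenteeism rates". The section on the health hygiene education intervention lists defecation in the open among the behaviours the programme aims to change. The Measurements section makes this questionnaire the source of individual risk factors and possible confounders. The Study design section has it repeated at the end of the four-month follow-up.

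**The concern.** Both items take a latrine at home for granted. The form allows for the opposite case when it asks about behaviour, since item 18 lets a child report always defecating in the open. It makes no such allowance when it asks about the household facility. For a child without a home latrine, none of the listed answers to items 15 and 16 applies. The interviewer can tick don't know, leave the item blank, or tick an untrue answer such as Outside with an invented drainage type. Different interviewers may choose differently.

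What is at stake is the description of household sanitation in the determinants analysis. Its lowest level would either be treated as missing or be merged with homes that do have a latrine. A later analysis plan cannot supply an answer category that the form did not offer.

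**Working it through.** The protocol gives no figure to reproduce, so the check compares the answer boxes item by item and then asks what item 18 can recover.

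**1. Boxes offered (same in Annex 5 and Annex 6)**

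| Item | Subject | Filter question first? | None / not-applicable / other box? |
|---|---|---|---|
| 13A-B | Source of water | Yes (13A) | Not applicable and Others |
| 15 | Latrine location | No | None |
| 16 | Latrine drainage | No | None |
| 18 | Open-air defecation | Not needed | Never is an answer |
| 27 | Footwear at home | Not needed | A box for wearing none |

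Items 7B, 20B-C, 21B-C, 28 and 29B also carry a not-applicable box, and item 9 has an Others box. The form therefore uses such answers routinely; items 15 and 16 are exceptions to its own practice.

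**2. What can be recorded for four kinds of child**

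| Child | Items 15-16 | Item 18 |
|---|---|---|
| No home latrine, always uses open ground | No applicable answer | Always: correct |
| No home latrine, uses a neighbour's | No applicable answer for the home | Never: correct |
| Home latrine, sometimes uses open ground | Correct | Sometimes: correct |
| Home latrine, always used | Correct | Never: correct |

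Item 18 is right in every row, so the behaviour is captured. It does not identify the facility: never covers children with and without a home latrine, and always or sometimes does not prove that the home has none. The Spanish wording also explains open ground as garden or yard, which may not bring to mind waste passed into the river from a house on stilts or a floating platform.

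**3. Where the two variables are used**

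- Secondary objective iv, as household determinants.
- The adjusted model in Planned statistical analyses, which names gender, sex, age and school ecological zone and adds other baseline characteristics only if they are unbalanced between arms.
- Not in the primary outcome, which comes from stool examination, nor in the randomisation or the power calculation.

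**4. Scale**

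The protocol gives no share of homes without a latrine. From Sample size justification, expected participants at baseline are 1438 × 0.806 = 1159, and after 5% loss 1159 × 0.95 = 1101. Each 1% of homes without a latrine is then 0.01 × 1159 ≈ 12 children at baseline and 0.01 × 1101 ≈ 11 at follow-up. Over a purely assumed range of 5% to 20%, the counts are 58 to 232 at baseline and 55 to 220 at follow-up. This shows scale only; it is not an estimate.

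**The case against.** The strongest reply is that little is lost. Item 18 asks every child about open-air defecation, with no skip, and that is the behaviour the programme targets. The section on location describes floating and land-based latrines; poor sanitation is not the same as no latrine, and the answers in item 16 suit what is described there. The form is administered by an interviewer, has a comments field, is to be pre-tested and is checked daily. A child would rarely not know whether the latrine is indoors, so don't know in item 15 together with always in item 18 would be a fair hint that there is none.

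Much of this stands. It rules out several stronger readings that a reader might infer:

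- That children who defecate in the open are lost or misclassified on that exposure. They are not, because item 18 records it.
- That the adjusted treatment effect will be wrong. Sanitation is not a named covariate and enters only if unbalanced at baseline.
- That a particular dilution of the sanitation effect can be calculated. This would need the share without a latrine and the infection rates by sanitation level, and the protocol gives neither.
- That nothing can be recovered later. Comments, daily checks and item 18 allow partial recovery.

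What the reply does not remove is the gap itself. Item 18 measures habit, not facility. The daily review concerns unclear answers and which ones are eligible, and for this child none is. Recovery from comments or from patterns of codes would depend on how each interviewer happened to deal with the case.

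**Conclusion.** The point holds in a narrow form. In both language versions, items 15 and 16 have no valid answer for a child without a home latrine, and only the latrine location and drainage variables are affected. The consequence is imprecision in one secondary objective, for a number of children the protocol does not allow one to estimate. If every home in the sample has a latrine, nothing is lost. The conclusion assumes that the forms are used as printed and that interviewers have no separate coding instruction for this case; none is stated. This is a minor point, worth acting on because the correction is nearly free before fieldwork.

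**What to change.** Before the baseline survey, in both Annex 5 and Annex 6:

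- Item 15: add a coded answer, No latrine at home, distinct from Inside, Outside and Don't know.
- Item 16: add Not applicable, to be ticked when item 15 is No latrine at home.
- Check both answers in the pre-testing phase already planned under Measurements.
- In the determinants analysis, keep No latrine as its own category and do not treat it as missing.

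The cost is one extra box on each of two items in each language, a codebook entry and a short instruction to interviewers. It needs no additional visits, staff or specimens.
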